### Cost Consequence Analysis

The economics of the revised Move More Pack will take the form of a cost consequence analysis, with costs assessed against a range of outcomes. Although this will not draw definitive conclusions regarding cost effectiveness, it will identify the costs of achieving the reported outcomes. The development costs and other costs needed to make the revised Move More Pack usable will not be included.

### Data Management

Web-based questionnaires will be completed using software from Qualtrics, USA. The questionnaire software from Qualtrics, USA, treats data as highly confidential [62] and offers the highest levels of data security [63]. Ownership, control, and management of data remain with the University of Surrey.

Information gathered will be secured on password-locked computers and the servers at the University of Surrey. Hard files will be stored in locked cabinets within the university. Project data, for example, consent forms, will be retained for at least 6 years and research data for at least 10 years as stipulated by the policies of the University of Surrey [64]. Personal data will be secured and processed in the strictest confidence according to the Data Protection Act [65].

Data for analysis and reporting is anonymized. Identifiable data are accessible only by the principal investigator, members of the research team, and authorized personnel from the University of Surrey, and regulatory authorities for monitoring purposes.

### Ethical Considerations

The information included in the revised Move More Pack is certified by the NHS England Information Standard [37]. The NHS England Information Standard ensures that publically available information has undergone rigorous assessment, is evidence-based, of high quality, clear, accurate, and appropriate for its intended audience. The revised Move More Pack does not prescribe exercise. The relevant safety information is sent to participants in the first postal communication. Criteria for cessation of physical activity is provided, for example, sudden onset of dizziness, chest pains, a racing heartbeat, breathing problems, nausea, unusual back or bone pain, muscle weakness or a persistent headache, advising participants to contact their doctors for these or other symptoms. Appropriate screening is in place within the study procedures to identify participants needing medical permission before increasing their physical activity, with these participants being excluded from this study. A log of participant issues will be maintained throughout the study, and participants will be offered a phone debriefing session at the end of the study.

Participants in the control arm will not be restricted with regard to being physically active. The participants in the control arm will be asked as part of the questionnaire instructed at the 12-week follow-up time point if they have used the revised Move More Pack within the previous 12 weeks, with their data omitted from the study if they have. This study received ethical approval from the University of Surrey Research Ethics Committee on March 15, 2017, reference UEC/2017/023/FHMS.

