The revised Move More Pack retained the physical activity and cancer booklet (Multimedia Appendix 2). A pull-out wall chart is included in the revised Move More Pack for users to track their progress, record achievements, and serve as a visual prompt to be more active (Multimedia Appendix 3). Furthermore, five activity leaflets (Multimedia Appendix 4) are included on popular activities of gardening, walking, and recreational swimming; the sports of badminton, bowls, cycling, golf, and walking football; and finally, on how to be generally active in daily life [38]. A digital versatile disc that focuses on exercise specifically for cancer survivors is included and is also available to view on the Web [39].

Tailored multi-component interventions are likely to be most effective in effecting lifestyle behavior change in cancer survivors [35,40,41]. Users of the revised Move More Pack can sign up to receive e-newsletters, with messages tailored to their reported prediagnosis levels of physical activity, and influenced by the stages of physical activity behavior change advanced by Marcus and Forsyth [42]. Prediagnosis levels of physical activity are collected using the Godin Leisure Time Exercise Questionnaire (GLTEQ) [43]. Case studies included within the e-newsletters are tailored to the age and gender of the user of the revised Move More Pack. A welcome email is sent to users of the revised Move More Pack, followed by e-newsletters sent during months 1, 2, 3, 6, 9, and 12. Details are outlined in Table 1, with an example e-newsletter included as Multimedia Appendix 5.

An online social community aims to link users of the revised Move More Pack, enabling social learning and enhancing social norms [44]. An online *ask the physio* group is available and allows users of the revised Move More Pack to post questions on an open forum to a registered cancer specialist physiotherapist [45]. Details of how to find local physical activity opportunities are also included on the Web [46].

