### Design

This study is a two-arm waiting list RCT (ISRCTN 66418871) with embedded process evaluation, designed following guidance from the MRC for evaluating complex interventions [52]. Figure 1 shows the progress through the phases of this study. The control arm participants receive brief physical activity information and details of the UK guidelines for physical activity. Intervention arm participants receive brief physical activity information, the revised Move More Pack, directions to the Internet-based tools, as well as the e-newsletters as outlined in Table 1, up to and including the newsletter sent in month 3.

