### Sample size

NHS England [13] report that 23% of cancer survivors are active to the recommended levels for aerobic activity, 31% are inactive, and 46% are physically active but not to the recommended levels. NHS England [13] also reported that 18% of cancer survivors are interested in becoming more active. The sample size for this study has been calculated based on the assumption that the revised Move More Pack will increase the proportion of the sample achieving the aerobic physical activity guidelines by 18%. A sample of 82 participants will be required per arm for a one-tailed test, power of 80% with alpha set at 5%. A total of 99 participants will be recruited per arm to allow for a 20% dropout.

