#### Process Evaluation

Use of each component of the revised Move More Pack will be assessed using a 4-point Likert scale of often, sometimes, rarely, and never. The 4-point Likert scale is included as part of the questionnaire administered to the intervention arm at 12 weeks and the control arm at 24 weeks. Participants will also have the opportunity to add comments about their use and their perceived usefulness of the revised Move More Pack. At the 12-week time point, participants from the intervention arm will be stratified into two groups, those inactive before diagnosis and those moderately active or active before diagnosis. Five participants from each group will be randomly selected and interviewed by phone to gain a deeper understanding of their interaction with, and views of, the revised Move More Pack. This interview process is repeated in the control arm at 24 weeks.

Interviews will follow a semistructured format and will be conducted by the principal investigator. This format has been selected to ensure that data are collected on central topic areas of use and perceived usefulness of the components of revised Move More Pack while not restricting the flow of the conversation. In addition, the interviews will aim to gather data to situate the experience of using the revised Move More Pack within a broad social context. The interview topic guide is included as Multimedia Appendix 8.

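### The control arm's 12-week exposure question names only the pack, a term the protocol uses both with and without the Internet-based tools, so controls' use of the web tools alone may be missed

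*Protocol article*

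**What the plan says.** **What is tested.** Under Design, the intervention arm receives brief information plus "the revised Move More Pack, directions to the Internet-based tools, as well as the e-newsletters". The Abstract (Methods) and 12-Week Follow-Up likewise name the tools in addition to the pack.

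**What is reachable on the web.** The section The Move More Pack and its Revision says the exercise film can also be viewed online, and that a group allows users "to post questions on an open forum to a registered cancer specialist physiotherapist". It also describes an online community, apps, video case studies and e-newsletters.

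**What controls are asked.** Ethical Considerations says that the 12-week questionnaire asks controls "if they have used the revised Move More Pack within the previous 12 weeks". Those who say yes have their data omitted.

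**Where component use is measured.** Process Evaluation describes a 4-point scale, from often to never, for each component. It is "administered to the intervention arm at 12 weeks and the control arm at 24 weeks".

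**The concern.** The 12-week comparison between arms is the primary one. For that window, the article describes one exposure measure in controls: a question about the pack. The scale that separates components is given to the intervention arm at 12 weeks, but to controls only after they too have been sent the pack. Component use over the primary window is therefore recorded in one arm only.

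Exposure among controls is plausible. They are recruited through the same charity's email database and Facebook page. They must be Internet literate, they are told that a pack with Internet-based tools exists, and after randomisation they receive physical activity information and guidelines. A control could find the film or the forum without ever seeing the printed pack, and could reasonably not regard that as using the pack.

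If this happened, the control proportion classified as active would rise and the observed difference would shrink. A small or null result would then have two explanations that the trial's data could not separate: the intervention does little, or some controls received part of it.

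**Working it through.** **1. How the protocol uses the word pack**

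| Place | Relation of the tools to the pack |
|---|---|
| Abstract, Background | Pack is a printed resource with supporting Internet-based tools |
| The Move More Pack and its Revision | Pack was redeveloped as a printed resource supported by such tools |
| Discussion, limitations | Pedometer use is called a component of the pack; the earlier description makes this a downloadable app |
| Abstract, Methods | Tools named in addition to the pack |
| Design | Pack, directions to the tools and e-newsletters listed as three items |
| 12-Week Follow-Up | Controls are mailed the pack and, separately, directed to the tools |

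The first three rows support a broad reading of the exposure question and the last three a narrow one. The protocol does not say which applies.

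**2. Reproducing the planned sample size**

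Inputs from Sample size: "23% of cancer survivors are active to the recommended levels for aerobic activity", so the control proportion is 0.23. The assumed increase is 18 points, so the intervention proportion is 0.41. "A sample of 82 participants will be required per arm for a one-tailed test, power of 80% with alpha set at 5" per cent.

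For the pooled two-proportion z test without continuity correction, with mean proportion m = (0.23 + 0.41)/2 = 0.32:

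n = [1.645 × √(2m(1 − m)) + 0.842 × √(0.23 × 0.77 + 0.41 × 0.59)]² / 0.18²

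This gives n = 81.99, so 82 per arm. It matches the protocol, and power at 82 is 80.0%. The calculation contains no allowance for contamination.

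**3. Effect of undetected use by controls**

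The documents give neither of the next two quantities, so both are assumptions:
- c = share of controls who use the tools undetected
- f = fraction of the 18-point effect that they gain

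Control proportion = 0.23 + 0.18·c·f

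Difference = 0.18 × (1 − c·f)

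Power = Φ{[difference × √82 − 1.645 × √(2m(1 − m))] / √(p₀(1 − p₀) + 0.41 × 0.59)}, where p₀ is the diluted control proportion and m = (p₀ + 0.41)/2.

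For c = 20% and f = 0.5: p₀ = 0.23 + 0.18 × 0.10 = 0.248, the difference is 0.162 and m = 0.329. Power = Φ[(1.467 − 1.093)/0.6545] = Φ(0.571) = 71.6%.

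| c | f | Control proportion | Difference (points) | Power at 82 per arm |
|---|---|---|---|---|
| 0 | – | 23.0% | 18.0 | 80% |
| 10% | 0.5 | 23.9% | 17.1 | 76% |
| 20% | 0.5 | 24.8% | 16.2 | 72% |
| 30% | 0.5 | 25.7% | 15.3 | 67% |
| 20% | 1 | 26.6% | 14.4 | 62% |

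The row with f = 1 is an upper bound for that c, because it credits the tools alone with the effect of the whole intervention.

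**The case against.** The strongest reply is that the question may already cover the tools. Three places in the protocol use the term broadly, and Process Evaluation applies the use scale to each component of the pack. The article also paraphrases the item; the real questionnaire may list the components. This stands as far as it goes: it is not established that a control who used only the forum would answer no. But the protocol's other usage is equally plain, and a participant cannot be expected to resolve what the protocol leaves open. Nor does the reply touch the timing of the use scale, which the article states outright. Even on the broad reading, the question as described records whether the pack was used, not which components or how often.

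A reader might infer that contamination goes unmeasured altogether. The documents do not support that. Pack use is asked over exactly the primary window and the answer is acted on; the possible gap is use of the tools alone.

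A reader might also infer that all the tools are open to anyone. Only the web film and the forum are described in that way. The e-newsletters need sign-up, the community is meant to link pack users, and the linking web page is dedicated to them. Recruitment also gives some protection, because the study information does not mention physical activity. That protection weakens once controls receive physical activity information after randomisation.

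**Conclusion.** The point holds in a limited form. Over the 12 weeks that matter most, no component-level exposure is planned for controls, and the one question they get rests on a term used in two ways. Web-only use may be missed, and dilution could then not be distinguished from lack of effect.

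The size is unknown. The fall in power from 80% to about 72% depends on 20% of controls gaining half of the planned effect; it is an illustration, not a forecast. The planned 82 per arm is reproduced and is not in dispute here. The change is worth making because it costs little and bears on how the primary result is interpreted.

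**What to change.** In Process Evaluation and Ethical Considerations, give controls at 12 weeks the same component list and 4-point use scale as the intervention arm. The list should name the printed items, the film in either format, the online community, the physiotherapist group, the apps, the video case studies and the e-newsletters. Place it after the outcome items, so that it cannot influence them, and before the pack is released. Report component use by arm.

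The answers must not feed the rule that omits controls who used the pack. That rule already conflicts with the intention-to-treat analysis stated under Data Analysis, and a broader exposure question would remove more controls after randomisation. Keep all randomised controls in the primary comparison, and use exposure only descriptively or in a supportive sensitivity analysis.

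The cost is about a minute of extra burden for controls, in an online questionnaire that they already complete. The scale exists, and the items name tools that controls are about to be sent.

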### Exclusion Criteria

There are greater risks from being inactive than taking part in physical activity. The revised Move More Pack does not prescribe exercise in any way, and the relevant safety information is sent in the post to participants at the start of the study. The safety information is taken from the Macmillan Cancer Support Web pages [55] and has received the NHS England Information Standard [37]. However, those participants considered at high risk of injury are excluded from this study. On the basis of guidance on exercise and cancer survivorship from the American College of Sports Medicine [7,56], reviewed and approved by subject experts from Macmillan Cancer Support’s physical activity team, the following screening questions will be asked of participants, with an answer of yes to any question resulting in exclusion from the study:

Are you less than 8 weeks postsurgery?Are you experiencing extreme fatigue, anemia, or severe balance and coordination problems?Do you have cancer in your bones or bone thinning?Do you have a heart or lung condition (excluding lung cancer)?Do you feel pain in your chest at rest, during your daily activities, or when becoming active?Do you have persistent pain in your muscles, bones, or joints?Do you have swelling or inflammation in the abdomen, groin, or lower extremity?Has your doctor ever said that you should only do medically supervised physical activity?Are you pregnant?

Excluded participants will be informed that they will need medical approval before becoming more physically active and, therefore, are not eligible for this study. They will be thanked for their time and given the details of how to order the free resources offered to participants in this study, for use after receiving permission from their general practitioners or cancer care teams, should they decide to become more active.

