### Data Analysis

The quantitative data will be analyzed using intention-to-treat analysis. The GLTEQ provides a physical activity score, and these scores can be used to categorize participants into inactive, moderately active, and active groups. The two-proportion *z* test is used to investigate differences between the proportions of participants in the control arm and the intervention arm classified as active.

Secondary analysis of the paired before and after ordinal data within each intervention arm will be analyzed with the Wilcoxon’s signed-rank test; across arms, comparisons will be analyzed with the Mann-Whitney *U* test. The mean GLTEQ scores will be analyzed with the independent *t* test and the paired *t* test. The predictors of self-efficacy and prediagnosis physical activity on post-intervention physical activity levels will be assessed by multiple regression analysis. Additional quantitative data will include descriptive statistics such as means, standard deviations, medians, and percentages.

The interviews will be recorded and transcribed verbatim. The interview transcripts and the qualitative comments made by the participants as part of the questionnaires administered at the 12-week and 24-week time points will be thematically analyzed [61] by two of the study investigators, ensuring that identified themes are grounded in the original data. A third investigator will be used where there are differences in opinion. The process of analysis will follow five stages:

Familiarization with the data involving reading and rereading the interview transcripts and qualitative comments.Initial coding.Theme identification.Theme review and development of higher level categories.Identification of relationships and patterns.

The investigators will move back and forth through these steps until they concur and are satisfied with the themes, categories, relationships, and patterns identified.

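### Omitting control participants who report using the pack contradicts the stated intention-to-treat analysis and leaves the 12-week error rate unassured

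*Protocol article*

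**What the plan says.** The protocol article makes two statements about who is analysed.

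- **Data Analysis:** "The quantitative data will be analyzed using intention-to-treat analysis". The comparison that follows is a two-proportion z test of "differences between the proportions of participants in the control arm and the intervention arm classified as active".
- **Ethical Considerations:** "The participants in the control arm will be asked as part of the questionnaire instructed at the 12-week follow-up time point" whether they have used the revised pack during the preceding 12 weeks, "with their data omitted from the study if they have".

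The omission is from the study as a whole, so as worded it reaches the primary test and every secondary analysis. It is not described as a per-protocol or sensitivity analysis. The article has no matching rule for intervention participants who leave the pack unused.

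**The concern.** Intention-to-treat keeps every randomised participant in the arm to which they were allocated, whatever they then do. The omission rule selects on behaviour that occurs after allocation, in the control arm only, and learns of it in the same follow-up round that supplies the 12-week outcome. The controls who remain are no longer the randomised counterpart of the full intervention arm.

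If controls who use the pack are more active than other controls, removing them lowers the control proportion and widens the apparent benefit, even when the pack has no effect. The result at stake is the main 12-week comparison, tested one-sided in the direction of benefit.

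**Working it through.** **1. The two statements side by side.** One section keeps all randomised participants as allocated; the other drops some controls because of what they did after allocation. Both cannot hold, and no other section reconciles them. This step needs no assumption.

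**2. Reproduce the plan's own figure.** The Sample size section gives "23% of cancer survivors are active to the recommended levels for aerobic activity", an 18% increase, a one-tailed 5% test, 80% power and 82 per arm. Reading the increase as percentage points, the proportions are 0.23 and 0.41, with mean 0.32:

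n = [1.645 × √(2 × 0.32 × 0.68) + 0.842 × √(0.23 × 0.77 + 0.41 × 0.59)]² / 0.18² = (1.0851 + 0.5448)² / 0.0324 = 81.99, which rounds up to 82.

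The stated 82 reproduces (pooled variance, no continuity correction), so 0.23, 0.41 and 82 serve as the base below.

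**3. Effect of the omission when there is no true difference.** Let c be the share of controls omitted and q the proportion of those users who are active. Neither is in the protocol. I assume c = 5%, 10% and 20%, and q = 15%, 23% (same as other controls), 41% (the plan's target rate) and 60%. With 23% active in each full arm:

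- proportion active among retained controls: r = (0.23 − c × q) / (1 − c)
- spurious difference: d = 0.23 − r
- probability of rejection: Φ[(d − 1.645 × SE₀) / SE₁], with 82 × (1 − c) controls against 82 intervention participants, SE₀ pooled and SE₁ unpooled

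Worked case, c = 10% and q = 41%: r = (0.23 − 0.041) / 0.90 = 0.210; d = 0.020; SE₀ = 0.0665; SE₁ = 0.0664; (0.020 − 0.1094) / 0.0664 = −1.347; rejection probability 8.9%.

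| Users active (q) | c = 5% | c = 10% | c = 20% |
|---|---|---|---|
| 15% | −0.4 points; 4.4% | −0.9; 3.8% | −2.0; 2.7% |
| 23% | 0; 5.0% | 0; 5.0% | 0; 5.0% |
| 41% | +1.0; 6.7% | +2.0; 8.9% | +4.5; 16.2% |
| 60% | +2.0; 8.9% | +4.1; 15.4% | +9.3; 41.1% |

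Each cell gives the spurious difference in percentage points (positive favours the pack), then the one-sided error rate.

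**4. Cost of keeping everyone when the pack works.** Take non-user controls at 23%, user controls at 41% and the intervention arm at 41%. The control proportion is 0.41c + 0.23(1 − c):

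- c = 10%: 0.248, difference 16.2 points
- c = 20%: 0.266, difference 14.4 points

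The plan recruits 99 per arm and allows for 20% dropout; 99 × 0.80 = 79.2, so about 79 remain. At 79 per arm, power is about 79% with no contamination, 70% at c = 10% and 61% at c = 20%. With the omission rule, the same settings give about 77% and 74%.

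**The case against.** The strongest defence is that the size, and even the sign, of any bias is unknown. That stands. The protocol gives no contamination rate and no activity figure for control users. If users are as active as other controls there is no bias; if they are less active it runs against the pack. A reader might infer that the rule is certain to favour the pack and inflate the error rate. The protocol supports only a conditional statement.

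Two further readings go too far.

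- **That any control who gets hold of a pack is removed.** The rule is triggered by reported use. A control who obtains a pack and does not use it stays in.
- **That control use is documented as likely.** The Exclusion Criteria section says that people screened out are "given the details of how to order the free resources offered to participants in this study". This shows that the resources are free and can be ordered; it does not describe information given to controls. The Recruitment section also keeps physical activity out of the invitation. Controls do receive brief activity information after allocation (Design section), so use is feasible, but no rate can be drawn from the text.

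It can also be said that the rule protects the contrast from dilution. It does hold power higher when the pack works (step 4), but by giving up the randomised comparison. None of these points removes the contradiction.

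**Conclusion.** The contradiction is real and stands on the text alone: followed as written, the plan produces a primary comparison that is not intention-to-treat, because controls are dropped for behaviour after randomisation and intervention participants are not. The one-sided error rate therefore cannot be assured at 5%.

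The expected direction, though not an established one, is towards the pack. Controls who find and use an activity pack may be more motivated, and the Aims section hypothesises that the pack raises activity. The sizes in step 3 rest on the assumed ranges for use and users' activity, on the plan's 23% and 82 per arm, and on a normal approximation. Because the rule defines the population for the main result and is simple to correct, it should be resolved before analysis.

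**What to change.** Delete the omission rule from Ethical Considerations and state in Data Analysis that every randomised control participant is analysed in the control arm whatever their reported pack use. Keep the 12-week question and use it to report the contamination rate. If an analysis without control users is wanted, label it a per-protocol sensitivity analysis. A complier-average estimate is optional; it needs further assumptions and would rest on one self-reported item.

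The textual change is about one sentence. The statistical cost is the dilution in step 4, which is not negligible: at 10-20% control use the 18-point difference shrinks to 16.2-14.4 points and power falls by roughly 9 to 18 percentage points (from 79% to 70-61%). The plan should state that cost, since the present sample size allows for dropout only.
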